## Abstract

**Background:**

Stereotactic ablative body radiotherapy (SABR) is a non-invasive alternative to surgery to control primary renal cell cancer (RCC) in patients that are medically inoperable or at high-risk of post-surgical dialysis. The objective of the FASTRACK II clinical trial is to investigate the efficacy of SABR for primary RCC.

**Methods:**

FASTRACK II is a single arm, multi-institutional phase II study. Seventy patients will be recruited over 3 years and followed for a total of 5 years. Eligible patients must have a biopsy confirmed diagnosis of primary RCC with a single lesion within a kidney, have ECOG performance ≤2 and be medically inoperable, high risk or decline surgery. Radiotherapy treatment planning is undertaken using four dimensional CT scanning to incorporate the impact of respiratory motion. Treatment must be delivered using a conformal or intensity modulated technique including IMRT, VMAT, Cyberknife or Tomotherapy. The trial includes two alternate fractionation schedules based on tumour size: for tumours ≤4 cm in maximum diameter a single fraction of 26Gy is delivered; and for tumours > 4 cm in maximum diameter 42Gy in three fractions is delivered. The primary outcome of the study is to estimate the efficacy of SABR for primary RCC. Secondary objectives include estimating tolerability, characterising overall survival and cancer specific survival, estimating the distant failure rate, describing toxicity and renal function changes after SABR, and assessment of cost-effectiveness of SABR compared with current therapies.

**Discussion:**

The present study design allows for multicentre prospective validation of the efficacy of SABR for primary RCC that has been observed from prior single institutional and retrospective series. The study also allows assessment of treatment related toxicity, overall survival, cancer specific survival, freedom from distant failure and renal function post therapy.

**Trial registration:**

Clinicaltrials.gov
NCT02613819, registered Nov 25th 2015.

## Background

### Renal cell carcinoma and SABR

Primary renal cell carcinoma (RCC) is the 9th most common cancer in Australia [1] and 8th most common worldwide [2]. In Australia there has been an 88% increase in the age-standardised incidence of RCC in the period from 1982 to 2014 [1]. The standard of care for fit patients with localised kidney cancer is surgical resection of the kidney (nephrectomy). However, patients undergoing partial or total nephrectomy for renal cancer experience post-operative nephron loss, which may result in new chronic kidney disease or advancement of pre-existing renal dysfunction [3, 4]. Additionally, since the mean age of onset is 65 years [1], many patients have coexisting medical issues that preclude them from major surgery. Presently, these patients have limited curative treatment options. Non-surgical treatment options for this population of patients include radiofrequency ablation (RFA) and cryotherapy. These thermal techniques have significant limitations. They can typically only treat smaller tumours which need to be away from the collecting system and vascular structures due to the risk of heat sink effects, stricture and/or fistula development [5]. Treatment of larger tumours poses significant risks of haemorrhage, which can require a nephrectomy to control [5]. Both RFA and cryotherapy are costly and dependent on user technician proficiency and availability. Both are invasive, with access through incisions in the skin. Thus, patients with inoperable primary RCC, particularly those with larger tumours, represent a group in need of an effective non-invasive alternative to surgery.

Stereotactic ablative body radiotherapy (SABR) is emerging as a non-invasive method for precision irradiation of tumours using doses with a higher biological effect than can be achieved with conventional radiotherapy. SABR does not necessitate inpatient hospital admission, is delivered in a single or relatively few treatment sessions, and is typically associated with a low toxicity and excellent local control rates in a variety of malignancies [6]. This radioablative technique represents a radical departure from conventional fractionated radiotherapy that is delivered with many treatments (fractions) over several weeks. SABR offers patients who are unable or unwilling to undergo surgery an effective alternative which can potentially prolong survival. SABR is now well established and widely utilised in the treatment of tumours of the brain, lung, liver, and spinal column [7–10].

In order to test this potential benefit of this technique in a larger randomised study, the initial step is to robustly establish efficacy of SABR for primary RCC. This multicentre phase II trial aims to validate the efficacy readout previously established by a pilot study conducted in the Australian setting [11].

### Existing knowledge

RCC is generally considered “radioresistant” in the context of conventionally fractionated radiotherapy. However, the capacity to deliver ablative doses of radiation accurately with SABR has shifted this paradigm [12]. The Karolinksa Institute in Sweden have the first reported clinical cases utilising SABR in the treatment of renal tumours, having treated kidney targets since the early 1990’s [13]. Wersall et al. [35] reported a retrospective series of 50 patients with metastatic renal cancer and 8 patients with inoperable primary tumours treated with SABR. Using a dose fractionation of 8Gy × 4, 10Gy × 4 and 15Gy × 3 they achieved a local control rate of 90–98%. 39% of patients developed at least one side effect, with 50% of registered side effects being grade I-II. In 2012 our group published a systematic review of 126 patients indicating favourable early results from SABR for primary RCC, with local control rates ranging from 84 to 100% and severe treatment related toxicities (grade 3+) of 3.8% [14]. Modern single institutional prospective reports from our centre [15, 16] and collaborators [17–19] corroborate these findings with very infrequent severe treatment related toxicities (< 5%). These studies report local control rates of 87% in 15 patients [19], 95% in 19 patients [17] and 100% in 30 RCC patients [18]. These findings are summarised in Table 1. A further recent study addressed the role of SABR in large primary RCC (those with a median tumour diameter of 9.5 cm) [20]. With a median follow up 3.9 years, there was one treatment related grade 3 event but no grade 4 or 5 toxicities. Importantly, in these studies, unlike RFA and cryotherapy, SABR was not limited to smaller tumours (< 4 cm) or those located away from central pelvic calyceal structures. Finally, the International Radiosurgery Oncology Consortium for the Kidney (IROCK) [21] published pooled results of 223 patients in 2018, with a 2-year local control rate of 97.8% [22].

**Table 1 Tab1:** Review of SABR literature for primary RCC

Author / Year	Patients	Follow-up (months - Median or Mean)	Average marginal dose (Gy)	Outcome - Crude Local control	Estimated 2 year LC	Overall Survival Median	Toxicities
Chang et al. [7] 2016	16	19	30-40Gy in 5 fractions	100%	NR	NR	1 grade 2 acute toxicity and 2 grade 4 late toxicities
Gilson et al. [8] 2006	33	17	Median 40Gy in 5 fractions	94%	92	NR	NR
Lo et al. [9] 2014	3	21.7	40Gy in 5 fractions	100%	NR	NR	Early: 1 x Grade 1 nausea Late: nil
McBride et al. [10] 2013 (abstract) [prospective]	15	36.7	Median 33Gy in 3 fractions	87% 1 failure at 30.7 mo 1 failure at 31.2 mo	NR	NR	1 x Grade 3 renal toxicity 5 x Grade 1 fatigue 2 x Grade 1 nausea
Nair et al. [27] 2013	3	13.3	39Gy in 3 fractions	100%	NR	NR	Early: 1 x Grade 1 nausea Late: Nil
Nomiya et al. [28] 2008	10	57.5	Median 4.5Gy x 16fx	100%	100	5 year OS 74%	10% Grade 4 toxicity, no other toxicities > Grade 1
Qian et al. [29] 2003 (abstract)	20	12	40Gy in 5 fractions	93%	86	NR	NR
Pham et al. [15] 2014 [prospective]	20	6	26Gy in 1 fraction 42Gy in 3 fractions	NR	NR	NR	60% Grade 1–2 No Grade 3, Grade 4
Ponksy et al. [30] 2015 [prospective]	19	13.7	Max 48Gy in 4 fractions	NR	NR	NR	5.2% Grade 2, 15.8% Grade 3–4
Siva et al. [16] [prospective]	33	24	26Gy in 1 fraction 42Gy in 3 fractions	97%	100%	2 year OS 92%	78% Grade 1–2 3% Grade 3
Svedman et al. [31] 2006 [prospective]	5	52	40Gy in 4 or 5 fractions, 45Gy in 3 fractions	80%	91	Median survival 32 months	89% Grade 1–2, 4% Grade 3
Svedman et al. [32] 2008	7	39	40Gy in 4 fractions	86%	91	NR	58% Grade 1–2, nil else
Teh et al. [33] 2007 (abstract)	2	9	24Gy–48Gy in 3–6 fx	100%	100	NR	NR
Staehler et al. [18] 2015 ^b^ [prospective]	30^a^	28.1	25Gy in 1 fraction	98% (at 9mo) ^b^	NR	Not attained after median 28.1 months^**+**^	13% Grade 1–2 nil else
Wang et al. [13] 2014	9	38.3	36-51Gy to 50% isodose line at 3-5Gy per fraction	5 year LC 43%	NR	5 year OS 35%	Early: 44% Grade 1 (GI, haem.) Late: 22% Grade 2 (GI)
Wersall et al. [34] 2005	8	37	40Gy in 4 or 5 fractions, 45Gy in 3 fractions	100%	100	Median survival 58+ months	20% Grade 1–2, 19% Grade 3, nil Grade 4+

^a^ report included an additional 15 patients with Transitional cell carcinoma;

^b^ pooled results with patients treated for TCC

*NR* not reported, *Gy* Gray

### Addressing an unmet clinical need

As RCC is a disease typically of an older population, in routine clinical practice some patients are not fit for surgery due to existing co-morbidities. These patients need an effective non-invasive alternative to surgery to control their kidney disease. A multicentre, multinational clinical trial is warranted to assess the efficacy of SABR as a treatment option for primary RCC in medically inoperable patients or those who decline surgery.

## Methods/design

### Study objectives and hypothesis

The primary objective of this study is to estimate the efficacy of SABR for primary RCC. The primary endpoint is freedom from local progression, as defined by lack of progression of the target lesion (primary RCC) as measured by RECIST criteria [66]. The primary hypothesis of this study is that freedom from local progression at 1-year post-treatment will be > 80%.

Key secondary endpoints include assessment of a) Toxicity, as measured by CTCAE v4.03; b) Overall survival; c) Cancer specific survival; d) Freedom from distant failure; e) Renal function measured by serum creatinine and estimated glomerular filtration rate (eGFR) using CKI-EPI equation, split function and calculated glomerular filtration rate (GFR) on nuclear medicine testing; f) Cost-effectiveness. An exploratory objective is to assess the utility of multi-parametric MRI (mpMRI) as a biomarker of treatment response in a subset of patients.

This trial will be conducted in radiation oncology treatment centres throughout Australia, the MAASTRO clinic in the Netherlands, and the Royal Marden Hospital in England. All participating centres must successfully complete pre-trial quality assurance procedures prior to enrolling patients to the study. This will consist of an initial credentialing phase involving phantom dosimetry audit, facility questionnaires and a plan quality benchmarking exercise. Real-time quality assurance through plan reviews will be performed as part of the trial.

### Study design

The Trans-Tasman Radiation Oncology Group (TROG) 15.03 FASTRACK II clinical trial is a single arm, multi-institutional phase II study conducted in collaboration with the Australian and New Zealand Urogenital and Prostate Cancer Trials Group (ANZUP). The trial will recruit 70 participants over a 3-year period, with patient follow-up to 5 years from the end of accrual. All participants will receive SABR as definitive treatment for their primary RCC.

The study population is patients with biopsy confirmed primary RCC with a single lesion within a kidney. The intervention is a single fraction SABR with one of two fractionation schedules selected based on tumour size: a single fraction of 26Gy is used for tumours ≤4 cm in maximum diameter, with 42Gy in three fractions delivered for tumours > 4 cm in maximum diameter. While biological equivalent dose estimation based on linear quadratic formula can be unreliable to estimate the effect of doses >10Gy per fraction, this model is still the most commonly used to describe iso-effectiveness of alternate SABR fractionation regimens. The radiosensitivity of the two most common human RCC cell lines (Caki-1 and A498) has been observed in the laboratory to vary with α/β values estimated to be 2.6Gy or 6.9Gy, depending on the cell line [23]. The biological effective dose for tumour effects when using the dose/fractionation cohorts proposed with an α/β of 6.9Gy are 123Gy for 26Gy in 1 fraction, and 127Gy for 42Gy in 3 fractions. When altering the model to use the alternate α/β of 2.6Gy, the biological equivalent dose is 286Gy for 26Gy in 1 fraction and 268Gy for 42Gy in 3 fractions. These dose calculations show that the cohorts are relatively iso-effective across a reasonable range for potential tumour effects in the study.

### Inclusion / exclusion criteria

To participate in the trial, patients must meet all of the following key inclusion criteria at randomisation:Age ≥ 18 years oldBiopsy confirmed diagnosis of RCC with no more than a single lesion within a kidney (bilateral RCC is allowable ECOG performance ≤2Life expectancy > 9 monthsEither medically inoperable, technically high risk for surgery or decline surgeryProvide written informed consentA multidisciplinary decision has been made that active treatment is warranted

Key exclusion criteria are listed below:Pre-treatment estimated glomerular filtration rate < 30 mls/minPrior systemic therapies for RCCPrevious high-dose radiotherapy to an overlapping region (defined as BED >40Gy using an α/β ratio of 10)Tumours larger than 10 cm in maximum dimensionDirect contact of the target tumour with bowelUntreated prior malignancy, or prior malignancy within 2 years of screeningVisceral / bony metastatic diseaseHorseshoe kidney

### Sample size and study duration

In total, 70 patients are required for this study. It is anticipated that it will take 36 months to complete target accrual. The sample size of 70 patients was chosen to provide sufficiently narrow confidence intervals for clinical outcomes. If up to 15% of participants do not proceed to treatment, or die or are lost to follow-up before experiencing a local progression in the first year, and assuming the freedom from local progression (FFLP) at 1-year is 90%, the corresponding two-sided 95% confidence interval will be 79–96%. A 1-year freedom from local progression of 80% or less will be considered undesirable and not worthy of proceeding to a future randomised study against other treatment modalities. The freedom from local progression at 1-year is expected to be around 90%. With those assumptions, the proposed sample size will have 80% power with 10% alpha to test the null hypothesis that the FFLP at 1-year is 80% or less. The study end date is deemed to be the date of last data capture, which will be when the final participant completes the 5 year follow-up visit. Participant assessments are tabulated in Table 2.

**Table 2 Tab2:** Participant Assessments

ASSESSMENTS	Pre-Registration^a,b^	Post Treatment^c^													Post Progression^f^
		4 wks	3 mths	6 mths	9 mths	12 mths	18 mths	24 mths	33 mths	42 mths	51 mths	60 mths	Annually thereafter^d^	Progression^e^	Annually
Informed Consent	✓														
Informed consent for Health Economics data^g^	✓														
CT (Thorax/Abdomen)	✓^h,i^			✓	✓	✓	✓	✓	✓	✓	✓	✓	✓	✓^h,i^	
Split Renal Function Test (DMSA SPECT/CT) and calculated GFR (Cr-51 EDTA) ^j^	✓					✓		✓		✓		✓	✓^j^		
Whole body bone scan	✓													✓	
Clinical Consultation	✓		✓	✓	✓	✓	✓	✓	✓	✓	✓	✓	✓	✓	
Eligibility confirmation	✓														
Blood Tests^k^ and eGFR ^l^	✓	✓	✓	✓	✓	✓	✓	✓	✓	✓	✓	✓	✓	✓	
QLQ-C30 questionnaire ^m^	✓	✓	✓	✓	✓	✓	✓	✓	✓	✓	✓	✓			✓^m^
Adverse Event Reporting	✓	✓	✓	✓	✓	✓	✓	✓	✓	✓	✓	✓	✓	✓	
Survival Status															✓
MRI Sub study^n^															
Informed Consent	✓														
Multiparametric MRI	✓		✓			✓									

^a^To be done within 8 weeks of registration

^b^Treatment to commence within 6 weeks of registration

^c^Calculated from the date of the last radiotherapy fraction given. Post treatment follow-up to continue until both local and distant progression has been recorded

^d^After participant has both local and distant progression documented, annual survival status will be collected

^e^To be done at both local and distant progression

^f^After participant has both local and distant progression documented, annual survival status will be collected until study closure

^g^Australian Participants only for consent to access outpatient medical and pharmaceutical services via the MBS and PBS

^h^With or without contrast

^i^CT to include pelvis at pre-registration & progression scans. The target lesion size determined from the pre-registration scan CT will dictate the fractionation schedule to be prescribed

^j-^ Where split function cannot be performed by DMSA SPECT/CT, a MAG-3 study should be performed

- Calculated GFR through Cr-51 EDTA measurement or equivalent should be performed at this time point whenever possible, if this study is available

- This should be the same study for all investigations time points

- After the 60 month post follow-up visit, these are to be performed biennially until study completion

^k^Blood test include - full blood count (FBE), serum urea and electrolytes (UEC’s), c-reactive protein (CRP) and estimated glomerular filtration rate (eGFR)

^l^Determined by the CKD-EPI equation

^m^QLQ-C30 questionnaire is to be completed post progression until participant reached 5 years post treatment

^n^Participating sites only

### Radiotherapy treatment regimen

All participants are to be adequately immobilised using, at a minimum, a half body vacuum immobilisation device. A 4DCT scan in treatment position is used to account for respiratory motion. Target volumes accounting for respiratory motion and setup uncertainty must be defined as below:Internal Target Volume (ITV) – The ITV must be contoured taking the total tumour excursion through respiration into account.Planning Target Volume (PTV) – ITV to PTV margins must take into consideration set-up uncertainties. A 5 mm expansion isotropic expansion from ITV to PTV must be used.

For fractionated treatment schedules, treatment fractions are expected to be delivered on non-consecutive days (approximately 48 h apart). All treatment should be completed within 3 weeks.

### Dose criteria

The investigational treatment will be prescribed to the covering isodose, ensuring that 99% of the PTV is covered by 100% of the dose (D99PTV = 100%). In the circumstance where doses to organs at risk (OAR) cannot be respected whilst achieving this level of coverage, an alternative prescription coverage of D95PTV = 100% is acceptable. The peak dose (DMax) should be ideally 125%, resulting in a normalised equivalent covering isodose of 80%. The acceptable isodose at the periphery is expected to be between 70 and 80%. Peak dose (Dmax) should not exceed 143%. OAR constraints are found in Table 3.

**Table 3 Tab3:** Organ at Risk Constraints

Organ	Parameter	Dose / Fractionation	
		26Gy/1Fx	42Gy/3Fx
Spinal canal	Maximum dose	0.03 cc < 12Gy point dose	0.03 cc < 18Gy point dose
Skin (5 mm subcutis)	Maximum Dose (1.5 cc)	< 18Gy	< 30Gy
Small Bowel	Maximum Dose / Volume	0.03 cc <26Gy 5cc < 22.5Gy Aim for <13Gy to full circumference of small bowel loop	0.03 cc < 30Gy 30cc ≤ 12.5Gy
	Maximum dose covering full circumference of bowel wall	≤12.5Gy	≤22.5Gy
Large Bowel	Maximum Dose (1.5 cc)	ALARA, aim for <26Gy	ALARA, aim for <42Gy
Stomach	Maximum Dose Maximum Volume	1.5 cc < 15.4Gy 5 cc ≤ 22.5Gy	0.03 cc < 30 Gy 5 cc ≤ 22.5Gy
Liver	Mean dose, Maximum Volume	No constraint, but mean dose and dose to 700 cc to be documented	700 cc < 15Gy
Ipsilateral kidney minus ITV	Maximum Dose (1.5 cc), V10Gy	ALARA: Minimise volume of high dose regions (> 50% isodose)^a^	ALARA: Minimise volume of high dose regions (> 50% isodose)
Contralateral Kidney	V10Gy	≤33%	≤33%

^a^ Ipsilateral Kidney minus ITV should adhere to the ALARA principle. In particular, investigators should focus on minimising high dose regions (> 50% isodose) outside the ITV but within the ipsilateral kidney

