### On-trial quality assurance (QA) program

This trial includes a comprehensive on-trial QA program. A pre-treatment radiotherapy QA technical review will be undertaken by the trial management team to provide independent validation of target definition, OAR contouring and plan quality. Post-treatment radiotherapy QA technical review will also be undertaken for all participating cases.

To ensure high plan quality and adherence to OAR dose limits, treatment plans will be assessed using knowledge based planning (KBP) prior to treatment. A RapidPlan model in the Eclipse treatment planning software (Varian Medical Systems, Palo Alto, USA) will be created based on the first 55 kidney SABR patients treated at Peter MacCallum Cancer Centre. The model will be applied to the first 20 patients recruited to the current trial to determine applicability to various planning systems and techniques used in this multi-centre trial. The model will then be used to determine if sufficient sparing of OARs has been achieved for each patient enrolled in the trial, based on previously achieved plan quality. This information will be communicated to the individual centres with the option to change the treatment plan prior to treatment if deemed appropriate given potential plan quality improvements and time and resource limitations.

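### In Table 3's single-fraction column, small bowel has two different full-circumference values, and one of the two stomach limits can never bind

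*Protocol article*

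**What the plan says.** All the entries at issue are in Table 3 of the protocol article, under Dose criteria, in the 26Gy/1Fx column.

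- **Small bowel, dose/volume row:** "0.03 cc <26Gy 5cc < 22.5Gy Aim for <13Gy to full circumference of small bowel loop". The last part is a full-circumference value, worded as an aim.
- **Small bowel, next row:** labelled "Maximum dose covering full circumference of bowel wall", with ≤12.5Gy for 26Gy/1Fx and ≤22.5Gy for 42Gy/3Fx.
- **Stomach:** "1.5 cc < 15.4Gy 5 cc ≤ 22.5Gy".

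For comparison, the 42Gy/3Fx column gives stomach "0.03 cc < 30 Gy 5 cc ≤ 22.5Gy" and small bowel "0.03 cc < 30Gy 30cc ≤ 12.5Gy".

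The article uses these limits in two places. Under Dose criteria, the default is 99% of the PTV covered by the prescription dose; where organ-at-risk doses cannot be kept at that coverage, "an alternative prescription coverage of D95PTV = 100% is acceptable". Under On-trial quality assurance (QA) program, plans are assessed before treatment, with the stated purpose "To ensure high plan quality and adherence to OAR dose limits". The article gives no rule for ranking an aim against a maximum.

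**The concern.** Limits for one organ and one schedule should form a coherent set. An aim should be at least as strict as the maximum on the same quantity; otherwise meeting the aim does not ensure that the maximum is met. Dose limits at increasing volumes should fall; otherwise the limit at the larger volume does no work. The single-fraction column breaks the first expectation for small bowel and the second for stomach.

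At stake is consistency between centres. The limits decide when a plan may drop from D99 to D95 target coverage, so two readers working from different entries could disagree on whether that fallback is open. They could also record different adherence results for the same plan. The article reports eight sites open and two more being activated, so a correction would still reach plans not yet made.

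**Working it through.** The article states no calculated figure on this point, so there is none to reproduce. The check is of the table's logic.

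**Small bowel, 26Gy/1Fx.** Let d be the dose covering the full circumference. The two entries are d < 13 (aim) and d ≤ 12.5 (maximum), in Gy.

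| d (Gy) | Aim, d < 13 | Maximum, d ≤ 12.5 |
|---|---|---|
| 12.4 | met | met |
| 12.5 | met | met |
| 12.7 | met | failed |
| 12.99 | met | failed |
| 13.0 | failed | failed |

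The entries disagree for 12.5 < d < 13, a window of 13 − 12.5 = 0.5Gy. Every plan that meets the maximum meets the aim, so the aim adds nothing to it.

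**Stomach, 26Gy/1Fx.** Let D(v) be the lowest dose received within the hottest v cc of the organ. The hottest 5 cc contains the hottest 1.5 cc, so D(v) cannot rise with v:

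D(5 cc) ≤ D(1.5 cc).

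If the first limit is met, then D(5 cc) ≤ D(1.5 cc) < 15.4 < 22.5Gy. The second limit is therefore met with more than 22.5 − 15.4 = 7.1Gy to spare. Reading the entries as volumes above a dose gives the same result: if less than 1.5 cc receives 15.4Gy or more, less than 1.5 cc receives 22.5Gy or more, which is already below 5 cc.

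Conversely, a plan with D(5 cc) from 15.4 to 22.5Gy meets the 5 cc limit but must fail the 1.5 cc limit. The 5 cc entry cannot reject any plan that the 1.5 cc entry accepts.

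**Comparison with the neighbouring pairs.** In a coherent pair the dose limit falls as the volume rises.

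| Organ and schedule | Smaller volume | Larger volume | Limit falls? |
|---|---|---|---|
| Small bowel, 1Fx | 0.03 cc: 26Gy | 5 cc: 22.5Gy | yes |
| Small bowel, 3Fx | 0.03 cc: 30Gy | 30 cc: 12.5Gy | yes |
| Stomach, 3Fx | 0.03 cc: 30Gy | 5 cc: 22.5Gy | yes |
| Stomach, 1Fx | 1.5 cc: 15.4Gy | 5 cc: 22.5Gy | **no** |

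Only the single-fraction stomach pair runs the wrong way.

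**The case against.** The strongest reply is that nothing printed is impossible to satisfy. For both organs a plan that meets the stricter entry meets every entry, and for small bowel the two entries differ in force, one an aim and the other a maximum. That stands. A reader might infer that planners cannot tell which limit governs, or that the stomach cell contradicts itself. Neither follows: read literally, the 1.5 cc stomach limit and the small-bowel maximum decide. The difference in force does not explain the small-bowel entries, however, because the aim is the looser of the two. What stays open is which values were intended.

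A reader might also take the identical 5 cc stomach limit in both columns as a further error. The article does not support that. An equal figure is not in itself wrong; contralateral kidney V10Gy has the same limit under both schedules. Nor can the article's linear-quadratic calculation settle it. Its α/β values come from renal cancer cell lines and are used for tumour effect, no value is given for stomach, and Study design itself warns that the model can be unreliable above 10Gy per fraction.

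A third tempting step is to say that credentialing and the knowledge-based model score plans against Table 3. The article does not say so. The model's stated benchmark is plan quality achieved in earlier patients, and its results reach centres as an option to revise the plan. Only the general purpose of adherence to organ dose limits ties the pre-treatment assessment to these limits.

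Finally, the article condenses a fuller protocol that is not shown, and sites may work from a table without these entries. That stands too, and makes part of the fix conditional. Excluding tumours in direct contact with bowel may reduce how often the small-bowel limit matters, but it does not reconcile the two values.

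**Conclusion.** The point holds in limited form. In the 26Gy/1Fx column, the small-bowel full-circumference dose has two values 0.5Gy apart, with the aim looser than the maximum. The stomach pair contains a limit that cannot bind, which suggests that a volume or dose in that cell is not as intended. The small-bowel entries conflict for plans above 12.5Gy and below 13Gy; the stomach entries are incoherent but jointly satisfiable.

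Severity is moderate. These are working safety limits that bear on target coverage and plan review, so this is more than a clerical matter. It does not touch the primary endpoint, the hypothesis test, alpha, power or sample size. Toxicity is a secondary endpoint, but the article offers nothing from which an effect on it could be estimated, and none is claimed.

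The conclusion assumes that the entries are read under the right column headings. They parse consistently that way, although a displaced entry cannot be wholly excluded. It also assumes the usual reading of a volume/dose pair as a limit on the hottest part of the organ.

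**What to change.** The clinical team should reconcile two items in Table 3 with the full protocol and the source constraints: the two single-fraction full-circumference entries for small bowel, and the single-fraction stomach pair. The corrected table should not give one quantity two unreconciled values, and each stomach entry should be capable of binding. Which values hold is a clinical decision, and none is suggested here.

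If the working protocol carries the same entries, the correction should go to sites and the QA team, and single-fraction plans already accepted should be re-checked against the corrected limits. If the working protocol is already coherent, correcting the article is enough.

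The cost is a corrected table and, if needed, a site notice and a re-check confined to single-fraction plans. There is no statistical cost.
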